## APPENDIX 4. KIDDYCAT

## APPENDIX 5. QUESTIONS OF THE EQ-5D-Y-PROXY 1

## **APPENDIX 6. CHILDREN'S BEHAVIOR QUESTIONNAIRE (CBQ)**

## **APPENDIX 7. THE IMPACT OF STUTTERING ON PRESCHOOLERS AND PARENTS (ISPP)**

## APPENDIX 8. DATA COLLECTION POINTS: PARENT

How would you (parent) rate the child's stuttering severity today? / Comment évaluez-vous (en tant que parent) la sévérité du bégaiement de votre enfant aujourd'hui ? / Hoe zou u (ouder) de stotterernst van uw kind vandaag beoordelen?

Please put the slider on the line for your child's stuttering severity today with 0 = no stuttering, 1 = extremely mild stuttering and 9 = extremely severe stuttering. / Veuillez mettre le curseur sur la ligne à l'endroit correspondant à la sévérité du bégaiement de votre enfant aujourd'hui avec la sévérité de 0 = pas de bégaiement, 1 = extrêmement léger et 9 = extrêmement grave. / Zet de slider alstublieft op de lijn voor de stotterernst van uw kind vandaag met 0 = geen stotteren, 1 = extreem mild stotteren en 9 = extreem ernstig stotteren.

|                  |                                 |                                   |
|------------------|---------------------------------|-----------------------------------|
| No
stuttering | Extremely
mild
stuttering | Extremely
severe
stuttering |
|------------------|---------------------------------|-----------------------------------|

*Pas de bégaiement – bégaiement extrêmement léger - bégaiement extrêmement grave /  
Geen stotteren – extreem mild stotteren – extreem ernstig stotteren*

How satisfied are you (parent) with your child's communication in everyday speaking situations at the present time? / Dans quelle mesure êtes-vous (en tant que parent) satisfait de la communication de votre enfant dans la vie quotidienne ces moments-ci? / Hoe tevreden bent u (ouder) met de communicatie van uw kind in alledaagse spreesituaties op dit moment?

Please put the slider on the line with 1 = extremely satisfied and 9 = extremely dissatisfied. / Veuillez mettre le curseur sur la ligne avec 1 = extrêmement satisfait et 9 = extrêmement mécontent. / Zet de slider alstublieft op de lijn met 1 = Extreem tevreden en 9 = Extreem ontevreden.

|                        |                           |
|------------------------|---------------------------|
| Extremely
satisfied | Extremely
dissatisfied |
|------------------------|---------------------------|

*Extrêmement satisfait – Extrêmement mécontent /  
Extreem tevreden – extreem ontevreden*

## APPENDIX 9. COMPLIANCE & TREATMENT FIDELITY CHECKLISTS

**Compliance Checklist** *(to check whether parents are implementing the treatment)*

**Lidcombe Program**

**Date treatment session:** ...../...../.....

**Duration of the treatment session:** 30 / 60 / ..... minutes

Implementation of the treatment at home was

OR ☐ an agreed practice time at home and lasted ..... minutes. It was performed ... times since the previous treatment session

AND/OR ☐ applying a technique or advice throughout the day

☐ At least one parent attends the treatment session with the child

☐ The parent brings the severity ratings for the typical stuttering severity observed each day (outside of the practice conversations) since the previous treatment session

☐ The parent manages the treatment activity while remaining focused on the child's speech

☐ The parent identifies stuttering moments and only gives verbal contingencies for unambiguous stuttering or unambiguous stutter-free speech

☐ The parent gives verbal contingencies:

☐ correctly (in an immediate, accurate, genuine and positive way that does not disrupt the parent-child communication)

☐ mostly for stutter-free speech

☐ in a varied way regarding the wording, timing, and context

☐ frequently enough

☐ without negative reaction from the child

☐ The child is fluent most of the time during the practice sessions at home

☐ The parent implemented verbal contingencies at home during practice sessions during 10 to 15 minutes or during natural conversations.

☐ The verbal contingencies were only given by the parent who is trained to do so

**Treatment Fidelity Checklist** *(to check whether SLTs are implementing the treatment per protocol)*

**Lidcombe Program**

- ☐ The SLT and/or parent converse(s) with the child
- ☐ The SLT asks the parent to assign a SR score to this conversation and coaches the parent if necessary (difference of >1 SR)
- ☐ The SLT and the parent discuss about stuttering severity and treatment responsiveness during the previous week, based on the stuttering severity ratings brought in by the parents
- ☐ The SLT and the parent discussed on how the treatment was implemented during the previous week
- ☐ The parent demonstrates to the SLT how verbal contingencies were conducted during the previous week and the SLT provides him/her with feedback
- ☐ The SLT observes that the child is feeling comfortable during the treatment sessions and with the treatment that is implemented
- ☐ The parent and SLT discuss changes to procedures for the coming week (verbal contingencies, frequency, context, structure). If time permits (possibly not during the 30-minute treatment sessions), the SLT models them, the parent applies them during a game or a conversation with the child and the SLT gives feedback before deciding whether this new procedure can be applied at home
- ☐ The parent and SLT summarize the plan for the coming week

**Compliance Checklist** (*vérifier si les parents appliquent le traitement*)

**Programme Lidcombe**

**Date séance de traitement:** ...../...../.....

**Durée de séance de traitement :** 30 / 60 / ... minutes

Mettre en œuvre le traitement à la maison était

OU BIEN ☐ un temps de pratique convenu à la maison et a duré ..... minutes. Elle a été réalisée... fois depuis la dernière séance de traitement

ET/OU BIEN ☐ appliquer une technique ou un conseil tout au long de la journée

☐ Au moins un parent est présent à la séance de traitement avec l'enfant

☐ Le parent apporte l'échelle d'évaluation de la sévérité du bégaiement observée chaque jour (en dehors des conversations d'entraînement) depuis la séance de traitement précédente.

☐ Le parent gère l'activité de traitement tout en restant concentré sur le discours de l'enfant

☐ Le parent identifie les moments de bégaiement et ne donne des commentaires verbaux que pour un bégaiement non ambigu ou une parole non bégayée (non ambiguë).

☐ Le parent donne des commentaires verbaux :

☐ correctement (d'une manière immédiate, précise, authentique et positive qui ne perturbe pas la communication parent-enfant).

☐ principalement pour une parole sans bégaiement

☐ d'une manière variée en ce qui concerne la formulation, le moment et le contexte

☐ assez souvent

☐ sans réaction négative de la part de l'enfant

☐ L'enfant parle de manière fluide la plupart du temps pendant les séances de pratique à la maison.

☐ Le parent a mis en place des commentaires verbaux à la maison chaque jour pendant 10 à 15 minutes au cours de séances d'entraînement ou de conversations naturelles.

☐ Les commentaires verbaux n'ont été donnés que par le parent qui est formé pour le faire.

**Treatment Fidelity Checklist** (*vérifier si les logopèdes mettent en œuvre le traitement conformément au protocole*)

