## 8.10 Withdrawal criteria

### 8.10.1 Discontinuation of trial intervention (without withdrawal of consent)

During the entire treatment phase, the reason and date for drop-out of treatment or the reason, date for leaving the allocated treatment arm are recorded in the e-CRF as well as whether it was the PCWS's, the parent's or the SLT's decision.

Reasons for stopping trial intervention (protocol treatment) may include, but are not limited to:

- ☐ The PCWS and/or PCWS' parent do(es) not wish to continue with trial intervention
- ☐ Safety reasons (Checklist Safety Reporting)
- ☐ Compliance issues of the parent(s). If planned sessions are not attended by the PCWS and parent(s) without a valid reason, it is a compliance issue.

- (1) The SLT may work around holidays or real-life situations in which a PCWS and the parent(s) cannot attend the session for one or more times (eg., illness of a parent, transport issues for some time, ...). These postponed sessions are limited in number and the SLT prepares the PCWS and parent for this gap in treatment.

The PCWS and the parent(s) can miss treatment sessions at most for three consecutive weeks without a valid reason before they are asked to withdraw from the trial intervention.

- (2) The parent(s) are asked to implement the treatment at home. In the Mini-KIDS treatment arm, they agree on their involvement in the mandate. In the LP and SCBT treatment arm, they agree to implement the treatment daily at home for about 10 minutes (LP) or two to three times per week for 20 to 30 minutes (SCBT) for making speaking activities pleasant again. If the SLT records compliance issues that violates those listed in the compliance checklists for each treatment arm, these will be discussed by the Co-CI and CI. It may a reason for discontinuation.

- ☐ Treatment fidelity issues of the SLT

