The video analyst may notice that a SLT adds treatment techniques or omits treatment techniques for the treatment approach that s/he is delivering compared to the treatment fidelity checklists for each treatment arm in this trial. If the SLT does not follow the protocol for more than 80% for a treatment session that was recorded on video, the SLT will be asked to follow the protocol more rigorously. If the SLT does not follow the protocol for more than 80% for each session indicated on the treatment fidelity checklists for more than six sessions, the SLT is considered to drift from the protocolised treatment approach and may be withdrawn from the trial intervention. Because data collection points often have more than a 6-week interval, SLTs are asked to report problems with treatment fidelity.

☐ Other reason

The trial will be analysed on an intention-to-treat basis and per-protocol analysis (Mo et al., 2021). All PCWS who stop randomised trial intervention will remain in the trial for follow-up unless the parent explicitly withdraws consent for data collection.

A PCWS's parent who refuses some or all trial procedures will still be followed up with the data collection procedures that the PCWS's parent(s) is agreeing unless the PCWS's parent(s) explicitly withdraws consent.

If the parent(s) discontinues with the trial intervention and did not withdraw consent, the PCWS will leave the allocated treatment arm or will receive other stuttering treatment than the manualised TreatPaCS treatment approaches from the SLT. The SLT will provide a video recorded speech sample from during the treatment session and from home, and the scores on the KiddyCAT, EQ-5D-Y proxy 1 and ISPP-questionnaire at the set data collection points during the trial after randomisation.

When a PCWS discontinues the trial intervention, a letter to inform the trial procedures for discontinuation will be provided to the PCWS and his/her parent(s). The parent(s) may decide to withdraw consent if s/he is not willing to provide the follow-up data.

The details of discontinuation (reason) should be clearly documented in the PCWS's speech-language therapy file and in the eCRF.

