## 9.3 Trial procedures in the LP

All sessions in Stage 1 take 45 to 60 minutes according to the LP treatment guide (Onslow et al., 2021). Sessions of 45 to 60 minutes with parent and PCWS, however, are not reimbursed through the Belgian health care system, only sessions of 30 minutes. Therefore, in this study, one hour sessions were limited to the first six treatment sessions. These sessions are scheduled with one PCWS and his/her parent(s) alone (not in groups). The parent receives education about stuttering and is coached to implement the treatment techniques.

### 9.3.1 Stage 1

Stage 1 aims at reducing the stuttering of the PCWS to (near) zero levels of stuttering (Onslow et al., 2021). During stage 1, parents learn to provide verbal contingencies during daily, 10-minute practice sessions with their PCWS. For unambiguous stutter-free speech, parents can praise, acknowledge the stutter-free speech or formulate a request for self-evaluation to the PCWS. The practice sessions that the parent(s) implement at home aim to give the PCWS the opportunity to practise stutter-free speech. Therefore, activities are specifically chosen and need to be fun for the PCWS. When the verbal contingencies for stutter-free are provided appropriately and effectively, the verbal contingencies for stuttering are also introduced. These are an acknowledgement of the stuttering moment or a request for self-correction. If a PCWS fails to

correct himself, no further verbal contingency on the speech is given (but a praise for the try can be provided).

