**Lidcombe Programma**

**Datum van de therapiesessie:** ...../...../.....

**Duur van de therapiesessie:** 30 / 60 / ..... minuten

Het toepassen van de therapie thuis was

OFWEL ☐ een afgesproken oefenmoment thuis en duurde ..... minuten. Het werd... keer sinds de vorige therapiesessie uitgevoerd

OFWEL ☐ het toepassen van een techniek of advies doorheen de dag

☐ Ten minste 1 ouder volgt de sessie samen met het kind

☐ De ouder brengt de ernstscores voor de typische stotterernst van elke dag (buiten de oefengesprekken) mee van de afgelopen week (sinds de vorige sessie)

☐ De ouder voert het oefengesprek uit én blijft gefocust op de spraak van het kind

☐ De ouder identificeert stottermomenten en geeft enkel verbale contingenties voor onbetwistbaar stotteren en onbetwistbare stottervrije spraak

☐ De ouder geeft verbale contingenties:

☐ correct (onmiddellijk en op een accurate, gemeende en positieve manier zonder dat het de kind-ouder communicatie stoort)

☐ voornamelijk voor de stottervrije spraak

☐ op een gevarieerde manier (woordkeuze, timing en context)

☐ voldoende frequent

☐ zonder negatieve reactie van het kind

☐ Het kind is meestal stottervrij tijdens de oefengesprekken thuis

☐ De ouder geeft verbale contingenties thuis tijdens oefengesprekken van 10-15 minuten of tijdens natuurlijke gesprekken.

☐ De verbale contingenties werden enkel gegeven door de ouder die getraind is om ze te geven.

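### The Lidcombe Program checklists in Appendix 9 are not equivalent across their three languages, although section 11.3.2 uses them to establish the 80% per-protocol set

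*Protocol*

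**What the plan says.** Section 11.3.2 takes the per-protocol population as the first-instance set for the primary endpoint. It defines that set by 80% adherence and names the Appendix 9 compliance and fidelity checklists, completed at each session, as the way to establish it. Sections 8.9.1 and 8.9.2 set the same 80% for acceptable parent compliance and therapist (SLT) fidelity.

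The LP home item reads as follows in the three compliance checklists:

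- French: "commentaires verbaux à la maison chaque jour pendant 10 à 15 minutes au cours de séances d'entraînement ou de conversations naturelles"
- English: "The parent implemented verbal contingencies at home during practice sessions during 10 to 15 minutes or during natural conversations"
- Dutch: "De ouder geeft verbale contingenties thuis tijdens oefengesprekken van 10-15 minuten of tijdens natuurlijke gesprekken"

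The protocol body sets a daily dose. In section 9.3.1, "parents learn to provide verbal contingencies during daily, 10-minute practice sessions with their PCWS"; in section 8.10.1, parents in this arm are those of whom it is said that "they agree to implement the treatment daily at home for about 10 minutes (LP").

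The LP fidelity checklists differ in two ways. English and Dutch have a separate item on talking over how home treatment went since the last session; French has none. The French item on changes for the coming week asks the SLT to model only when a new verbal contingency is brought in. The English and Dutch items extend this to changes in contingencies, frequency, context or structure. All three ask for modelling only when time allows. Section 9.3.1 has the SLT model procedures that are new or altered, which agrees with English and Dutch.

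**The concern.** An adherence threshold is only as uniform as the form it is read from. Here the same session can be classed differently depending on the language of the form, and the forms have three stated uses:

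- **Primary per-protocol set (section 11.3.2).** LP is the comparator in both non-inferiority contrasts, so misclassification in that arm can touch both.
- **SLT drift (section 8.10.1).** A therapist who falls short "for each session indicated on the treatment fidelity checklists for more than six sessions, the SLT is considered to drift", and may be withdrawn from the trial intervention.
- **Review for discontinuation (section 8.10.1).** On parents' adherence the rule is: "compliance issues that violates those listed in the compliance checklists for each treatment arm, these will be discussed by the Co-CI and CI". Practice that is less than daily breaks a listed frequency only on the French form.

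Section 8.9.2 assigns French-language videos to a French-speaking analyst and Dutch-language videos to a Dutch-speaking one. If each uses the form in that language, the video check would not reveal the difference.

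**Working it through.** **Inputs.** The cut-off is 80% (sections 8.9.1, 8.9.2, 11.3.2). The item lists are the three LP versions in Appendix 9. Drift means more than six sessions, so seven (section 8.10.1). The protocol gives no worked checklist score, so there is no figure of its own to reproduce. One point per item is my assumption.

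**Item counts.** The fidelity list has 8 items in English, 8 in Dutch and 7 in French. The compliance list has the same number of items in each language: 8 if the five sub-items on giving contingencies count as one, 12 if they count singly without their heading, 13 if every box counts.

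**Pass marks** (smallest score at or above 0.80): 6/7 = 86%, 7/8 = 88%, 10/12 = 83%, 11/13 = 85%. None of these lists can score exactly 80%, so the 'at least' of section 8.9.1 and the 'more than' of section 8.10.1 give the same class.

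**Fidelity.** Let h = 1 if the item that French lacks is skipped, c = 1 if a changed but not new procedure is left unmodelled although time allowed, and k = the number of other shared misses. The English or Dutch score is (8 − h − c − k)/8 and the French score is (7 − k)/7.

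| h | c | k | English/Dutch | French | Same class? |
|---|---|---|---|---|---|
| 0 | 0 | 1 | 7/8 = 88% pass | 6/7 = 86% pass | yes |
| 0 | 0 | 2 | 6/8 = 75% fail | 5/7 = 71% fail | yes |
| 1 | 0 | 0 | 7/8 = 88% pass | 7/7 = 100% pass | yes |
| 1 | 0 | 1 | 6/8 = 75% fail | 6/7 = 86% pass | **no** |
| 1 | 0 | 2 | 5/8 = 63% fail | 5/7 = 71% fail | yes |
| 1 | 1 | 0 | 6/8 = 75% fail | 7/7 = 100% pass | **no** |

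The case h = 0, c = 1 gives the same scores as h = 1, c = 0.

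**Compliance, parent not practising daily, m other misses.** On N items the English or Dutch score is (N − m)/N and the French score is (N − 1 − m)/N.

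| N | m at which class differs | English/Dutch | French |
|---|---|---|---|
| 8 | 1 | 7/8 = 88% pass | 6/8 = 75% fail |
| 12 | 2 | 10/12 = 83% pass | 9/12 = 75% fail |
| 13 | 2 | 11/13 = 85% pass | 10/13 = 77% fail |

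At every other m the class agrees. Non-daily practice alone (m = 0) passes even in French: 7/8 = 88%, 11/12 = 92%, 12/13 = 92%.

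**Drift.** An SLT who regularly skips the item French lacks plus one other item scores 75% each time on the English or Dutch form and reaches the drift count at the seventh such session. On the French form the score is 86% each time and the count never starts.

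**Exposure.** The computed effect is confined to the LP arm: 83 of 249 children by section 11.1.

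**The case against.** Section 9.4 calls Appendix 9 an example and places the working compliance form in the SLT site file. The Trial Master File is also to hold compliance and fidelity manuals that are not shown, and these could fix the scoring. The rule for combining sessions into a child's 80% may lie in the SAP. All this stands as a limit on what can be shown about effect. It does not remove the mismatch, because section 11.3.2 cites Appendix 9 directly, and a later rule cannot recover an item the French form never collected.

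The daily commitment in section 8.10.1 binds LP parents whatever the form language. All three forms also have header fields for minutes and number of practices, and a sub-item that contingencies are given "frequently enough". So a reader who infers that dose goes unrecorded in English and Dutch would be wrong. What differs is the scored item.

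A reader might also infer that any of the fidelity differences leads to the drift count. For the item on changes this is too strong. Modelling is asked for only when time allows, which all three forms say may not be so in a 30-minute session, and section 9.3 limits one-hour LP sessions to the first six. Seven failing sessions by that route need at least one 30-minute session with time to spare, or sessions from several children.

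The inverse-probability weights do not answer the point. They address selection into adherence, not an adherence indicator read differently by form, and the covariates named in section 11.3.2 include neither language nor site. Minimisation by site should roughly balance language across arms, which limits the effect. It does not cancel it, because these items apply to LP only.

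**Conclusion.** The three LP versions are not equivalent in a scored dose item, in the number of fidelity items and in the scope of the item on changes. At one point per item this is enough to reverse the class of a session near 80%. The direction is mixed: French is stricter on home practice and more lenient on SLT fidelity.

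It would go too far to say that the primary comparison is biased in a known direction or by a known amount. The share of French forms and the rule for aggregating sessions are not given, so the number of children reclassified cannot be computed. The intention-to-treat analysis in section 11.3.3 does not use the forms. Nor is the shorter French list shown to be an error against the protocol: section 9.3.1 has no separate step matching the extra item, so this is a lack of equivalence, not a French omission. Severity is minor.

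**What to change.** Make the three LP versions in Appendix 9, and the matching site-file and REDCap forms, identical item by item:

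- State the daily Stage 1 practice dose in the home item in every language.
- Use one fidelity item set, either adding the missing item to French or dropping it from English and Dutch.
- Word the item on changes to cover both new and altered procedures, as section 9.3.1 does.
- Align the Dutch header, which reads as either/or, with the and/or of the English, and restore the missing number in the Dutch coaching item.

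Check Mini-KIDS and SCBT in the same pass. The Mini-KIDS item on a child's resistance covers home only in English but session and home in French and Dutch, and the Dutch SCBT home item loses the limit to the first three months. I have computed no effect for these. The translation and back-translation procedure that section 8.6 plans for the ISPP would serve.

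I would not rescore recorded sessions on a reduced item set, which would alter the pass rule, or derive dose from headers that are not themselves equivalent. The cost is a correction to the appendix and forms and a note to sites. No new data are needed.

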**Programme Lidcombe**

- ☐ Le logopède et/ou le parent converse(nt) avec l'enfant.
- ☐ Le logopède demande au parent d'attribuer un score ES à cette conversation et l'accompagne si nécessaire (différence de > 1 valeur ES)
- ☐ Le logopède et le parent discutent de la gravité du bégaiement et de la réponse au traitement au cours de la semaine précédente, sur la base des évaluations de la gravité du bégaiement apportées par les parents.
- ☐ Le parent montre au logopède comment les commentaires verbaux ont été mis en œuvre au cours de la semaine précédente, et le logopède donne un feedback.
- ☐ Le logopède observe que l'enfant se sent à l'aise pendant les séances de traitement et avec le traitement mis en œuvre.
- ☐ Le parent et le logopède discutent des modifications à apporter aux procédures pour la semaine suivante. Si le temps le permet (éventuellement pas pendant les séances de traitement de 30 minutes) et si une nouvelle contingence verbale est introduite, le logopède la modélise, le parent l'applique au cours d'un jeu ou d'une conversation avec l'enfant et le logopède donne son avis avant de décider si cette nouvelle contingence verbale peut être appliquée à la maison.
- ☐ Le parent et le logopède résument le plan de la semaine

**Compliance Checklist** (om na te gaan of ouders de behandeling volgens het behandelprotocol uitvoeren)

